**Appendix E**

**Preparation of mononuclear cells for DNA extraction and plasma separation and storage for later follow-up studies**

1. After collection, gently invert each tube 4 to 5 times to mix anticoagulant additive with blood.
2. Keep the tubes upright at room temperature until centrifugation. **Centrifuge blood samples within 1 hour of collection.**
3. Immediately before centrifugation, remix the blood sample by gently inverting the tubes 4 to 5 times.
4. Centrifuge in a temperature controlled (refrigerated) horizontal rotor, (swing-out head) centrifuge (18-20oC)for 20 minutes at 1700 x g .
5. After centrifugation, resuspend the cells into the plasma by inverting the unopened “green/red-top”CPT tubes gently 4 times remove stopper and transfer into a 15 ml polypropylene tube.
6. Centrifuge the tube containing the PBMCs and plasma at 1000 x g for 5 minutes.
7. Remove the supernatent containing the plasma and transfer to a 5 ml freezer vial.
8. Add 10 ml of PBS to the tube still containing the mononuclear pellet and resuspend with gentle vortex mixing.
9. Centrifuge the PBS tube containing the PBMCs at 1000 x g for 5 minutes. Repeat steps 8 and 9 one more time.
10. Resuspend the mononuclear cells in 1 ml of PBS with gentle vortexing.
11. Transfer the mononuclear cell suspension to a 1.5 ml Epindorf tube and store at –20oC.

**APPENDIX F**

**Monitoring of Collagen Cryptic Epitopes in Serum and Urine:**

Standard ELISA methods have been used in the development of the cryptic collagen ELISA Assay. Briefly, Mabs HUI77 or HUIV26 are immobilized on 96-well microtiter plates. The plates are next washed with buffer and incubated with 5% BSA in PBS for 1.5 hours to block non-specific binding sites. Serum samples are diluted in 1:2 in dilution buffer and 50µl is added to each well and allowed to incubate for 2 hours at room temperature. The plates are next washed 8 times with wash buffer and incubated with a biotinylated polyclonal antibody to collagen for 2 hours. The plates are washed again and incubated with HRP-conjugated anti-Biotin antibody for 2 hours. Finally, the plates are washed and peroxidase substrate is added. The optical density is measured at a wavelength of 492 nm. Serum and urine will be collected for monitoring at day 6 of each cycle following treatment. The amount of denatured type IV collagen in ng/ml will be assessed.

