1. OBJECTIVES

1.1 To assess the efficacy of BAY 43-9006, (anti-tumor effects and proportion of clinical responses), in stage IV malignant melanoma patients. .

1.2 To assess the relationship between efficacy of BAY 43-9006 and the presence of mutant BRAF and wild-type BRAF within the melanoma tumors.

1.3 To further characterize the known toxicity profile of BAY 43-9006 at the recommended phase II dose.

1.4 To determine in the first 13 patients of each subgroup if treatment with BAY 43-9006 disrupts the *RAS/BRAF/MEK/MAPK* pathway by depleting intra-tumor stores of BRAF and/or downstream proteins such as CDK4, phospho-erk, MAPK and cyclin D1.

1.5 To assess the relationship between serum cryptic collagen epitopes and extent of tumor burden, invasion and metastasis and potential of serum collagen epitopes to serve as a possible surrogate marker to monitor the course of disease following therapeutic intervention in all patients enrolled in the study.

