- 1. A variety of studies have suggested that cellular interactions with the Extracellular Matrix (ECM) can regulate a wide variety of cellular functions including adhesion, migration and proliferation (31). Angiogenesis, malignant tumor growth and metastasis all require proteolytic remodeling of components of extracellular matrix (32). Interestingly, three studies have suggested that cellular interactions with the Extracellular Matrix (ECM) can regulate a wide variety of cellular functions including adhesion, migration and proliferation (31). Angiogenesis, malignant tumor growth and metastasis all require proteolytic remodeling of components of extracellular matrix (32). Interestingly, recent studies have identified cryptic regulatory epitopes that are normally hidden within the three dimensional structure of the ECM protein collagen (33), (34). Under normal physiological conditions these cryptic epitopes of collagen are not exposed (33), (34). However, following proteolytic remodeling of the collagenous ECM during tumor growth and invasion these unique cryptic epitopes are exposed and can be recognized by two novel monoclonal antibodies termed HUIV26 and HUI77 (33), (34). The functional cryptic epitopes defined by these unique Mabs have been shown to be specifically associated with angiogenic blood vessels and proliferating tumors in vivo, while little if any was detected within normal tissues (33), (34). These findings suggest that exposure of these epitopes may correlate with induction of angiogenesis and tumor progression (33), (34). Interestingly, during collagen synthesis pro-peptide segments of the collagen chains are cleaved and released into the circulation as part of the collagen fibril formation. In fact, investigators have developed an ELISA based assay to quantify the levels of collagen pro-peptide and found a correlation with tumor growth and metastasis (35), (36). Based on these studies, the possibility that [name] laboratory’s unique cryptic epitopes of collagen could also be cleaved and released into the systemic circulation was tested. [name] and colleagues have developed an ELISA based assay to detect soluble HUIV26 and HUI77 cryptic epitopes that is based upon a sandwich assay employing the use of a biotinylated anti-type IV collagen polyclonal antibody along with an anti-biotin monoclonal antibody conjugated to horseradish peroxidase as depicted in Figure 7. This assay has been subjected to an extensive validation regimen and as shown in Figure 8 and has the necessary range of linearity and sensitivity to allow it to be amenable for the monitoring of a clinical protocol where serial samples will be monitored. Figure 9 also demonstrates the results of preliminary findings which indicate that the cryptic epitopes of collagen can be detected in serum from melanoma patients. Importantly, the levels of these cryptic epitopes were significantly elevated in serum from melanoma patients as compared to serum from normal subjects. These findings suggest the possibility that the levels of cryptic collagen epitopes may correlate with extent of tumor burden, invasion and metastasis. Thus, serum levels of these unique cryptic epitopes may be useful to monitor the course of diseases following therapeutic intervention. We will examine levels over the duration of treatment and will examine the relationship with the extent of tumor burden. (**Appendix F**)

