**8. STUDY CALENDAR**

Baseline evaluations are to be conducted no more than 1 week prior to administration of study agent. Scans and x-rays must be done no more than 4 weeks prior to the start of therapy. In the event that the patient’s condition is deteriorating, laboratory evaluations should be repeated no more than 48 hours prior to initiation of the next cycle of therapy.

|  | **Pre-Study (<14 days before starting drug)** | **Each cycle** | | | **Every 2 cycles** | **Off Study** |
| --- | --- | --- | --- | --- | --- | --- |
| **D1** | **D8*,15*,22*** | **D28** |
| BAY 43-9006 |  | X | X | X |  |  |
| **Informed consent** | X |  |  |  |  |  |
| **Demographics** | X |  |  |  |  |  |
| **Medical history** | X |  |  |  |  |  |
| **Physical exam** | X | X |  | X |  | X |
| **Vital signs** | X | X | X | X |  | X |
| **Height / Weight** | X | X |  |  |  | X |
| **Medications** | X | X |  |  |  | X |
| **Performance status** | X | X |  | X |  | X |
| **Hb, ANC, plts** | X | X |  |  |  | X |
| **Serum chemistry**** | X | X |  |  |  | X |
| **EKG** | X |  |  |  |  |  |
| **B-HCG** | X |  |  |  |  |  |
| **Adverse Events** |  | X |  |  |  | X |
| **Tumor Measurements** |  | X |  | X1 | X2 | X |
| **Collection of PBPC’s** |  | X |  | X |  | X |
| **Collagen Cryptic Epitopes** |  | X |  | X |  |  |
| **Tumor Biopsy** |  | X*** |  | X***† |  |  |
| **PT/INR if on therapeutic anti-coagulation** | X | X | X | X |  | X |

* Weekly blood pressures will be done for the first cycle.

**Electrolytes, calcium, magnesium, liver function tests (AST, ALT, total bili) and LDH.

*** Biopsies done only on Cycle 1.

† The post treatment tumor biopsy will be conducted 18-48 hours after the first treatment cycle.

1 Day 28 tumor measurements will be based on the measurement of tumors sites that can be assessed by clinical exam.

2 The every other cycle, day 28 tumor measurements will be assessed by imaging studies.

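### Collagen-epitope sampling days conflict: days 1 and 28 of each cycle in the study calendar, day 6 (with urine) in Appendix F, which alone would leave no pre-treatment sample

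*Protocol*

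**What the plan says.** Objective 1.5 concerns the relation of serum epitopes to tumour burden, invasion and metastasis, and the "potential of serum collagen epitopes to serve as a possible surrogate marker to monitor the course of disease", in all enrolled patients. Section 7 describes the intended use: "We will examine levels over the duration of treatment and will examine the relationship with the extent of tumor burden". It then refers to Appendix F.

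The sampling days are given in two places:

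- **Section 8, Study Calendar.** The row "Collagen Cryptic Epitopes" is marked at D1 and D28 of each cycle. The pre-study, D8/15/22, every-2-cycles and off-study cells are empty.
- **Appendix F.** "Serum and urine will be collected for monitoring at day 6 of each cycle following treatment".

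The calendar marks tumour measurements at D1, at D28, every 2 cycles and off study. Its footnotes add: "Day 28 tumor measurements will be based on the measurement of tumors sites that can be assessed by clinical exam" and "The every other cycle, day 28 tumor measurements will be assessed by imaging studies". Section 11.4 makes the analysis of correlative endpoints exploratory and descriptive.

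**The concern.** The two schedules share no sampling day, and nothing ranks one above the other. This is a multi-institution study (sections 10.1 and 10.4), so sites could follow different pages. Section 7 directs anyone running this assay to Appendix F, not to the calendar.

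A marker proposed for following disease under treatment is most informative with a level before treatment and levels close in time to tumour measurements. If some sites draw on days 1 and 28 and others on day 6, differences in level between sites are mixed with differences in time on drug. An analysis plan cannot repair this later, because a sample that was not drawn cannot be recovered.

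Urine is a second mismatch. It is in the title and the collection sentence of Appendix F. However, objective 1.5 names serum only, the calendar row does not mention urine, the Appendix F procedure describes dilution of serum only, and the standard curves in section 7 are for human serum.

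**Working it through.** The protocol states no figure to reproduce, so the check is day arithmetic.

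**Inputs**
- Cycle length 28 days: section 11.2 puts the end of the second cycle at 56 days.
- Appendix F draw: day 6 of each cycle, counting the first dosing day as day 1.
- Calendar draws: D1 and D28 of each cycle.
- Tumour measurements: D1 and D28 of each cycle, with imaging on D28 of every second cycle.
- Assumption: cycles run consecutively without delay.

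**Study days over six cycles** (c = 0, 1, …, 5)

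| Event | Formula | Study days |
|---|---|---|
| Appendix F draws | 28c + 6 | 6, 34, 62, 90, 118, 146 |
| Calendar draws | 28c + 1 and 28c + 28 | 1, 28, 29, 56, 57, 84, 85, 112, 113, 140, 141, 168 |
| Tumour measurements (any method) | 28c + 1 and 28c + 28 | same 12 days as the calendar draws |
| Imaging | every second D28 | 56, 112, 168 |

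**Results**
- Appendix F alone: the first draw follows 6 − 1 = 5 days of dosing, so there is no pre-treatment sample.
- Appendix F alone: 0 of 6 draws fall on a tumour-measurement day. Each is 5 days after the nearest one, the D1 measurement (6 − 1 = 5, 34 − 29 = 5, and so on).
- Appendix F alone, around the day-56 scan: the last earlier draw is 56 − 34 = 22 days before, and the next is 62 − 56 = 6 days after. The day-112 scan gives the same gaps (112 − 90 = 22; 118 − 112 = 6).
- Section 4.3 ends treatment at progression. A patient who stops at the day-56 scan may therefore not reach the day-62 draw, leaving samples on days 6 and 34 only.
- Calendar alone: 12 of 12 draws fall on a tumour-measurement day.

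**Limits of the calendar schedule.** The collagen row has no pre-study mark. D1 of cycle 1 is also the first dosing day, and the calendar does not say that the sample is pre-dose. In odd-numbered cycles the D28 measurement is by clinical examination only. Baseline scans may be up to 4 weeks before treatment, so even a D1 sample need not share a visit with the baseline scan.

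**The case against.** The strongest reply is that the two passages can be read as additive. Appendix F does not say that day 6 is the only draw, nor that it replaces section 8, and its sentence closes a description of assay method. A site doing both would draw on days 1, 6 and 28 and would lose nothing. That reading is possible, but nothing in the protocol states it and day 6 has no visit in the calendar. It shows that the loss depends on which page a site follows; it does not remove the conflict.

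A reader might infer that objective 1.5 cannot be met. The documents do not support that. The objective asks about a relationship and a possible surrogate, the planned analysis is descriptive, and no change-from-baseline or same-day analysis is specified. Serial day-6 levels would still describe the on-treatment course and could be related to a measurement 5 days earlier or a scan 6 days earlier.

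A reader might also quote gaps of 22 days to the D28 examination (28 − 6) and 50 days to the first scan (56 − 6). The subtraction is right, but it looks forward only from the cycle 1 draw and omits the D1 measurement and the day-62 draw.

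Finally, a reader might say that none of the planned 2 × 37 = 74 patients would have a baseline. That holds only if every site ignores the calendar. The opposite claim, that the calendar gives every patient a baseline, assumes a pre-dose draw that the calendar does not state.

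**Conclusion.** The point stands as an internal contradiction that should be reconciled. Sampling day and specimen type differ between section 8 and Appendix F, and neither is given precedence. For a site that follows Appendix F alone, the loss is the pre-treatment level, the change from baseline, and all same-day pairing with scheduled tumour measurements (0 of 6 draws over six cycles, against 12 of 12 under the calendar). Sampling on different days at different sites is a risk, not something the documents show to have happened.

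The consequence is a weaker exploratory objective 1.5. The response-rate endpoint, the two-stage boundaries and the sample size are untouched. The figures assume uninterrupted 28-day cycles and day 6 counted from the first day of each cycle.

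**What to change.** Amend Appendix F so that serum is collected at days 1 and 28 of each cycle, as in the study calendar, and state in both places that the cycle 1 day 1 sample is drawn before the first dose. Either delete the day-6 and urine collections, or add them to the calendar with a stated purpose.

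The amendment should not restrict the analysis to samples drawn at the same visit as a tumour measurement. Because baseline scans may precede treatment by up to 4 weeks, such a rule could discard the baseline pair.

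The cost is a short text amendment. Over six cycles, a site that was following Appendix F alone would go from 6 serum draws to 12, all at existing visits. A site that was doing both schedules would go from 18 to 12 if day 6 is deleted. Deletion gives up the early on-treatment value and the urine series, to which the protocol attaches no stated objective.

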**APPENDIX G**

**SAMPLE DATA COLLECTION FORM**

NYU 04- Guidelines for Data Collection

Patient Registration:

After patient has been screened for eligibility and signed an informed consent, Patient Registration and Eligibility Checklist forms will be sent via fax or email to the Coordinating Center. The Coordinating Center will return the Patient Registration form with the assigned patient id number.

A copy of the informed consent together with copies of source documents confirming eligibility will be sent via fax or mail as soon as possible after the patient is on-study.

Data Collection:

An EXCEL spreadsheet template will be sent electronically to each site. The information collected on the spreadsheet is entered into the NCI CDUS web-based application and submitted to the NCI quarterly on the following schedule:

Submission Deadline Period Covered

30 April 01 Jan - 31 Mar

31 July 01 Mar - 30 Jun

31 October 01 Jul - 30 Sep

31 January 01 Oct - 31 Dec

Updated spreadsheets will be sent to the Coordinating Center on a regular basis and at least 2 weeks before each NCI submission deadline.

In addition to the spreadsheet, copies of source documents will be sent via fax or mail to the Coordinating Center when a patient goes off-study or more frequently for responders.

# ON-STUDY REGISTRATION

| NYU 04- A Phase II Study of BAY 43-9007 in Stage IV Malignant Melanoma | | | |
| --- | --- | --- | --- |
| Date Submitted:  Mo / Dy / Yr ___/ ___/ ___ | NCI Protocol #: | Patient Initials: | |
| SEX:  [ ] M [ ] F | Date of Birth:  Day/ Mon / Yr  ___/ ____/ ___ | Age (yrs) | Ethnicity: |
| Body Weight (Kg) | | Height (cm) | |
| Method of Payment: | | Postal Code: | |
| Histology:  **Melanoma** | | Performance Status: | |
| Date of Diagnosis:  Mo / Dy / Yr: _____/ _____/ _____ | | Date On-Study:  Mo / Dy / Yr: _____/ _____/ _____ | |
| Prior Therapy  Chemo [ ] Y [ ] N Hormone [ ] Y [ ] N Immuno [ ] Y [ ] N  Radiation [ ] Y [ ] N Surgery [ ] Y [ ] N | | | |

Patient ID Number: _________________ (assigned at Coordinating Center)

Completed By:

Name: ____________________ Signature: ___________________ Date: ___/ ___/ ___

**Appendix H**

**Medication Diary**

| **Name** |  |  |  |  |  |  |
| --- | --- | --- | --- | --- | --- | --- |
| **1**  **AM_______**  **PM_______** | **2 AM_______**  **PM_______** | **3 AM_______**  **PM_______** | **4 AM_______**  **PM_______** | **5 AM_______**  **PM_______** | **6 AM_______**  **PM_______** | **7 AM_______**  **PM_______** |
| **8 AM_______**  **PM_______** | **9 AM_______**  **PM_______** | **10 AM_______**  **PM_______** | **11 AM_______**  **PM_______** | **12 AM_______**  **PM_______** | **13 AM_______**  **PM_______** | **14 AM_______**  **PM_______** |
| **15 AM_______**  **PM_______** | **16 AM_______**  **PM_______** | **17 AM_______**  **PM_______** | **18 AM_______**  **PM_______** | **19 AM_______**  **PM_______** | **20 AM_______**  **PM_______** | **21 AM_______**  **PM_______** |
| **22 AM_______**  **PM_______** | **23 AM_______**  **PM_______** | **24 AM_______**  **PM_______** | **25 AM_______**  **PM_______** | **26 AM_______**  **PM_______** | **27 AM_______**  **PM_______** | **28 AM_______**  **PM_______** |
